### Sample size

The sample size of 144 children represents 9 children per age group (<13y; 13 to 18y), GMFCS strata, and intervention combination. An additional 16 participants will be recruited to accommodate an estimated 10 % drop out rate (144/.9) for a total of 160. The 10 % drop out rate was based on the current 7 % drop out rate in the feasibility trial conducted at Holland Bloorview. Sample size calculations were based on pre- to post-intervention change on the primary outcome (Gross Motor Function Measure-66) (GMFM-66) [21] and a two-factor factorial design (F tests). For the GMFM-66 change score, assuming a Type I Error of 0.05 and 36 patients per group, the study will have 85 % power to detect an effect size of 0.25 for the RAGT group, 0.25 for the fPT group, and 0.25 for the interaction. Assuming a standard deviation (SD) of subjects of 10, these effect sizes correspond to an actual SD among appropriate means of 2.5. For the GMFM-66, Dimensions D and E, mean change scores of 5.3 (SD = 5.6) and 5.9 (SD = 7.1) have been reported after Lokomat® training [20] and 4.6 (SD = 7.1) for PT [27]. These numbers correspond to effect sizes of 0.9 (GMFM Dimension D), 0.8 (GMFM Dimension E) for the Lokomat®, and 0.6 (GMFM-66 score) for PT. However, a change of 3 points on the GMFM-66 is considered a clinically important difference [28]. Thus we have amplified our power to detect a small effect size (0.25) among groups. PASS [29] was used to calculate sample size. Recruitment will take place at the three sites Holland Bloorview (Toronto, Canada), Glenrose Rehabilitation Hospital (Edmonton, Canada) and the Rehabilitation Institute of Chicago (Chicago, U.S.) over a period of 4 years.

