### Randomization

Following the screening assessment, participants will be randomly allocated to one of the four groups using computer-generated random sequence with varied block sizes to prevent randomization pattern prediction by investigators and ensure balanced group sizes. Age (<13 y; 13 to 18 y), GMFCS level (II and III), and site (Holland Bloorview, Glenrose Rehabilitation Hospital, Institute of Chicago) will be used as stratification variables to ensure group balance. The random sequence will be uploaded into the RedCap randomization module [30].

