### Statistical analysis

Data will be described (e.g., means, standard deviations, frequencies) for each intervention group and each stratification variable. Graphical summaries will include mean plots and boxplots. Change scores (post minus pre, follow-up minus post) will be summarized for each outcome. For each change score and outcome, an ANOVA for the two-factor factorial design will test the effect of each factor (RAGT, fPT) and their interaction (RAGT*fPT) on mean change score. Confidence intervals (95 % CIs) will be reported for the mean of each intervention group. Further, mixed-effects multiple linear regression models will be developed for each outcome with centre as a random effect, centre by intervention as an interaction (to assess centre effect), and other important variables (e.g., age and GMFCS level) as covariates. Variables will be dropped from the model one at a time if *p* > 0.05, and residual diagnostics will assess model fit. This modeling will allow us to assess the effect of the interventions in the presence of important variables that were not balanced across intervention groups by randomization and also can easily deal with incomplete observation times. All main analyses will be based on intent-to-treat with secondary analyses of those with >80 % adherence to their intervention. R [52] will be used for statistical analysis by a data analyst blinded to intervention group.

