## Discussion

It is critical to know if children with cerebral palsy benefit from RAGT more than over-ground walking training programs and maintenance therapy alone. The results of this trial will provide important insight into the relative effectiveness of RAGT and functional physical therapy. We will measure a broad range of outcomes that could potentially be affected by RAGT, and we anticipate that the trial will provide information needed to guide clinical practice related to RAGT for children with cerebral palsy.

RAGT is currently used clinically at the Edmonton and Chicago sites and is used only for research in Toronto. We anticipate that we may encounter some challenges at recruitment at the two sites where RAGT is used clinically. Our primary concern is related to possibility of parents’ preference for clinical use of RAGT over the possibility of being randomly allocated to a control group. To mitigate this risk, we may inform parents of group allocation following the screening assessment and then will allow some flexibility in the timing of the baseline assessment. This flexibility will allow families to schedule according to group allocation. They may decide to access clinical RAGT after the control period and during the summer months, when many families request therapy. In addition, children in the control group will be able to access their choice of therapy upon completion of the study to mitigate the risk of drop outs due to allocation to the control group.

The qualitative component will enhance the interpretability of the quantitative data through data triangulation [73]. In addition, the inclusion of a qualitative component in this RCT will serve three key purposes. Firstly, it will provide insight into the subjective experience of children and their parents with the trial interventions and how their values regarding quality of gait and previous therapy may have shaped those experiences. Understanding these experiences is highly relevant to the implementation of gait-related interventions in clinical practice to ensure that children and parents are engaged, able and motivated to participate in therapy. Research in this area is lacking.

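### The ANOVA of change that sizes the trial adjusts for neither baseline GMFM-66 nor the stratification factors and uses only complete visit pairs; the mixed model does not secure these terms, and neither model is named primary

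*Protocol article*

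**What the plan says.** All references are to the protocol article.

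- **Statistical analysis, first model:** "Change scores (post minus pre, follow-up minus post) will be summarized for each outcome". For each of these, "an ANOVA for the two-factor factorial design will test the effect of each factor", namely RAGT and fPT, together with their interaction, on the mean change. No other term is listed.
- **Sample size:** "Sample size calculations were based on pre- to post-intervention change on the primary outcome", with two-factor F tests, "assuming a Type I Error of 0.05 and 36 patients per group", an effect size of 0.25 and 85% power. Recruitment is raised from 144 to 160 for 10% dropout.
- **Randomization:** age group, GMFCS level and site "will be used as stratification variables to ensure group balance".
- **Statistical analysis, second model:** mixed-effects regressions are then to be developed for each outcome. Centre is a random effect with a centre-by-intervention term, and age and GMFCS level are given as examples of covariates. Variables leave one at a time when p exceeds 0.05. The section says this modelling can deal with incomplete observation times.
- **Analysis set:** "All main analyses will be based on intent-to-treat". The section does not say which of the two models is a main analysis.

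**The concern.** The factors that govern allocation should be in the model that tests the treatment effect, and the pre-treatment value of the outcome is usually its strongest predictor. The only model here with a fixed form contains none of them as covariates. The model that could contain them has a form settled by the data: stratification factors may be removed on a significance test, and baseline is not named at all.

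Three things are at stake.

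1. **Precision.** Subtracting baseline imposes a slope of 1 on it. When the true slope is below 1, as it is with equal variances and a correlation below 1, the change score carries more noise than a baseline-adjusted analysis.
2. **Calibration.** Stratifying removes between-stratum variation from the arm comparison. An analysis without the strata leaves that variation in the error term, so its standard errors are too large.
3. **Analysis set.** A child without both visits of a pair has no change score. Because the two scores are post minus pre and follow-up minus post, a child who misses the post visit but attends at 3 months enters neither ANOVA. Taken alone, the ANOVA then falls short of all randomized children.

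With no primary model named, it is also open which result answers the trial's question.

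**Working it through.** **Inputs from the article.** N = 144 (4 × 36), alpha = 0.05, effect size f = 0.25 (SD among means 2.5, SD of subjects 10), 10% dropout.

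**Inputs assumed, because the article gives none.** Baseline-to-post correlation rho of GMFM-66, taken from 0.5 to 0.95, with equal variance s² at both visits. Share R² of the change variance explained by age group, GMFCS level and site, taken from 0.05 to 0.20.

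**1. The plan's own power.** Each factorial effect has 1 numerator df and 144 − 4 = 140 denominator df. Noncentrality = N·f² = 144 × 0.0625 = 9. The noncentral F gives power **0.846**, so the stated 85% is reproduced for the unadjusted ANOVA with 144 complete pairs. Recruitment: 144/0.9 = 160.

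**2. Baseline as a covariate.**
Variance of change = 2s²(1 − rho).
Residual variance given baseline = s²(1 − rho²).
Ratio = (1 + rho)/2.
The noncentrality becomes 9 ÷ ratio, with 139 denominator df.

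| Assumed rho | Ratio | Variance saved | Noncentrality | Power |
|---|---|---|---|---|
| 0.5 | 0.75 | 25% | 12.0 | 0.931 |
| 0.7 | 0.85 | 15% | 10.6 | 0.898 |
| 0.8 | 0.90 | 10% | 10.0 | 0.881 |
| 0.9 | 0.95 | 5% | 9.5 | 0.864 |
| 0.95 | 0.975 | 2.5% | 9.2 | 0.855 |

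**3. Stratification factors only.** They cost 4 df (age 1, GMFCS 1, site 2), leaving 136. Noncentrality = 9/(1 − R²). Power is 0.863, 0.881 and 0.915 at R² = 0.05, 0.10 and 0.20.

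**4. Both.** Variance factor = (1 + rho)/2 × (1 − R²), with 135 df. At rho = 0.9 and R² = 0.05 it is 0.95 × 0.95 = 0.9025, and power is 0.880. At rho = 0.9 and R² = 0.10 it is 0.855, and power is 0.896. Multiplying the two savings assumes that they do not overlap. GMFCS level and baseline GMFM-66 are likely to share information, so these figures are upper guides.

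**5. Test level when the strata are left out.** Under stratified allocation the effect estimate varies with (1 − R²) of the variance that the error term uses. With critical value c = 3.909 (F on 1 and 140 df), the actual level is about 2[1 − Φ(√(c/(1 − R²)))]. This gives 0.043, 0.037 and 0.027 at R² = 0.05, 0.10 and 0.20. The formula returns 0.048 rather than 0.05 at R² = 0, so it slightly overstates the effect. The direction is conservative throughout.

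**6. Missing visits.** At the planned dropout, 160 − 144 = 16 children would have no pre-to-post pair. The article does not say how many of them would attend at 3 months, so the number that a repeated-measures model would bring back cannot be computed.

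**The case against.** The strongest reply is that the same section already supplies an adjusted model. It includes centre, mentions age and GMFCS level, and is said to handle incomplete observation times. A condensed article may leave the final covariate list to a SAP that is not shown. Change scores do use baseline, and under randomization their analysis is unbiased. The trial is correctly sized for the test it names.

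Much of this stands, and it rules out several stronger readings:

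- **That the unadjusted ANOVA is the declared main analysis.** A reader may infer this from the sample size, but the article does not say it.
- **That baseline is ignored.** It is subtracted; what is missing is its use as a covariate.
- **That the trial is underpowered or its type I error inflated.** The 85% is reproduced, and leaving out the strata makes the test conservative.
- **That the plan expects control-arm dropout and the result is therefore biased.** The Discussion offers therapy of choice after the study "to mitigate the risk of drop outs due to allocation to the control group". That names a risk and a mitigation. Arm-related loss biases the comparison only if it also relates to outcome.
- **That a better model would win back 16 of 160 children.** Those are the planned losses, already covered by recruitment. A model with baseline only as a covariate recovers nobody who lacks every post-baseline visit.

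What the reply does not remove is the stated content of the two models. The ANOVA's terms are listed in full. The mixed model's drop rule is explicit and would apply to stratification factors. An unseen SAP could repair this only by changing what the article fixes.

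**Conclusion.** The point holds as a matter of efficiency and of pre-specification. The ANOVA that sizes the trial omits baseline adjustment and all three stratification factors, the mixed model does not guarantee any baseline, age or GMFCS term, and no primary model is named.

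The size is modest and depends on inputs that the article does not give. Baseline adjustment saves 10% of residual variance at rho = 0.8 and 5% at 0.9, which lifts power from 0.846 to about 0.88 and 0.86. The full range examined is 2.5% to 25%, and a high correlation makes the gain small. If the strata explain 5% to 20% of the change variance, the nominal 0.05 test runs at roughly 0.043 to 0.027. These figures rest on equal variances at both visits and on the assumed rho and R².

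Bias from complete-pair analysis is possible, but it has not been shown and cannot be sized from the article. The change is worth making because it gains precision at almost no cost.

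**What to change.** Name one primary model before unblinding:

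- **Terms:** RAGT, fPT and RAGT*fPT, baseline GMFM-66, age group, GMFCS level and site as fixed terms, all kept regardless of p-value. The rule that drops variables at p > 0.05 should not apply to this model.
- **Structure:** a repeated-measures model on all available visits, with the factorial terms crossed with visit and a within-child covariance. The post-intervention contrast should be primary, because the sample size is based on it. A child who misses the post visit but attends at 3 months then contributes.
- **Children with no post-baseline visit:** they are retained only if baseline is modelled as a response or missing values are imputed. State which applies, so that the intent-to-treat claim matches the analysis.
- **Supportive:** keep the unadjusted ANOVA of change, which ties back to the sample size calculation.

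The cost is wording in the protocol or SAP. The stratification factors are known at randomization and GMFM-66 is already measured before the intervention. Adjustment uses 5 denominator df in the single-visit calculation (140 to 135). The sample size need not change.

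### Centre has only three levels: fitting it as random with a centre-by-intervention term can leave the adjusted RAGT and fPT tests on 2 to 6 degrees of freedom, or let an underpowered pre-test choose the model

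*Protocol article*

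**What the plan says.** The first-listed analysis is on change scores and does not involve centre: "an ANOVA for the two-factor factorial design will test the effect of each factor (RAGT, fPT) and their interaction (RAGT*fPT" and so on. The Statistical analysis section then adds mixed-effects regression models for each outcome, "with centre as a random effect, centre by intervention as an interaction (to assess centre effect", with covariates such as age and GMFCS level. A selection rule follows: "Variables will be dropped from the model one at a time if *p* > 0.05".

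Three other places bear on this. Sample size: "Recruitment will take place at the three sites Holland Bloorview (Toronto, Canada), Glenrose Rehabilitation Hospital (Edmonton, Canada) and the Rehabilitation Institute of Chicago". Randomization: age, GMFCS level and site "will be used as stratification variables to ensure group balance". Discussion: "RAGT is currently used clinically at the Edmonton and Chicago sites and is used only for research in Toronto".

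The article does not say whether the centre-by-intervention term is fixed or random. Nor does it say whether intervention there means each factor or the four-level group, or whether the drop rule covers the interaction.

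**The concern.** The three centres are named and fixed by design; they are not a sample from a population of centres. A variance estimated from three levels has 2 df. When centre is random, its interaction with a fixed factor is conventionally random too. The treatment effect is then judged against how much it varies from site to site, and three sites say very little about that.

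These models supply the covariate-adjusted effects, are the only stated analysis that accounts for the stratification factors, and are meant to handle incomplete observation times. They could disagree with the factorial ANOVA merely because of how centre was handled, and the effective error term could change from one outcome to the next. The Discussion gives a concrete reason why sites might differ (clinical use of RAGT at two, research use only at the third). A fixed site factor describes that directly.

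The stated purpose is also loose: a centre-by-intervention term assesses whether the treatment effect differs across centres, not the effect of centre itself.

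**Working it through.** **Inputs from the Sample size section.** "assuming a Type I Error of 0.05 and 36 patients per group" (four groups, N = 144), f = 0.25, SD 10, SD among means 2.5 (a 5-point difference between factor present and absent), stated power 85%. **Assumption:** equal sites, 144/3 = 48 children each, 12 per group per site. The article gives no numbers per site.

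**1. Reproduce the plan's figure.** Noncentrality = N × f² = 144 × 0.0625 = 9. The noncentral F with 1 and 140 df gives power 84.6%, which agrees with the stated 85%.

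**2. Same effect, different error terms, no true site heterogeneity.** SE of the RAGT main effect = 10 × √(4/144) = 1.667.

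| Treatment of centre | Denominator df | Critical t | Power | 95% CI half-width |
|---|---|---|---|---|
| Centre fixed, no interaction | 144 − 4 − 2 = 138 | 1.98 | 84.6% | 3.30 |
| Centre-by-group fixed | 144 − 12 = 132 | 1.98 | 84.6% | 3.30 |
| One random centre-by-group variance, kept | (3 − 1)(4 − 1) = 6 | 2.45 | 70.7% | 4.08 |
| Random centre-by-factor term, kept | (3 − 1)(2 − 1) = 2 | 4.30 | 38.7% | 7.17 |

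The row with centre-by-group fixed holds for the effect averaged over sites. If the software reports the effect at one reference site, its SE is 10 × √(4/48) = 2.89 and it answers a different question.

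**3. Chance in the variance estimate.** With no true heterogeneity, the interaction variance is estimated as zero with probability P(F < 1): 63% on 2 df, 57% on 6 df. If the drop rule does not cover the interaction, and the test uses 2 df when the estimate is positive and pooled error otherwise, simulated power is 54%.

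**4. If the drop rule covers the interaction.** The sampling variance of a site-specific RAGT effect is 4 × 100/48 = 8.33. The SD of the true effect between sites is not in the article; 0, 2 and 4 points are assumed here. Simulation (200,000 runs, balanced; interaction dropped if p > 0.05, otherwise 2 df):

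| Between-site SD of effect | Interaction dropped | Type I error | Power for 5 points |
|---|---|---|---|
| 0 | 95% | 4.7% | about 80% |
| 2 | 87% | 9% | 69% |
| 4 | 65% | 16% | 47% |

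The type I error here refers to a zero mean effect over a population of centres, the target implied by a random centre. Even at an SD of 4 points, the pre-test misses the heterogeneity in 65% of trials.

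**5. The centre intercept.** Its variance is also estimated as zero in about 63% of analyses when centres do not differ. Treatment varies within centre, so in a balanced layout the treatment estimate is the same either way. Pooling changes the SE by at most 1 − √(138/140), about 0.7%.

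**The case against.** A reader might infer that all treatment tests in this trial rest on 2 df, or that the planned 85% power is lost. The documents support neither reading. The stated power belongs to the factorial ANOVA, which has no centre term; the mixed models are additional. Only centre is labelled random, and a random intercept alone costs no treatment df. The 2-df result needs the interaction to be random, split by factor and kept. With one pooled variance it is 6 df; with a fixed interaction it is about 132.

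The drop rule weakens the low-power reading further. If it covers the interaction, the term usually goes and power is about 80%, so 39% and 54% would not describe the procedure. A reader might also take the frequent zero estimate of the intercept variance as damaging; step 5 shows that it is not. Finally, coding and the df method are details that an article commonly leaves to the analysis plan, and their absence is not criticised here.

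All of that stands, and it makes the consequence conditional. The choice the article does state remains: a three-level stratification factor is random, with an interaction attached, under a p-value selection rule. Each way of carrying this out has a cost: few df, a treatment model chosen by a weak pre-test, or coefficients that depend on coding.

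**Conclusion.** The concern holds in conditional form and is limited to the adjusted models. For f = 0.25 with equal sites and no true heterogeneity, power is about 39% (2 df) or 71% (6 df) if a random interaction is kept, against about 85% with centre fixed. If the drop rule removes the interaction, power is about 80% without heterogeneity. Type I error for the mean effect over centres is then about 9% or 16% if the effect truly varies between sites with an SD of 2 or 4 points, values assumed here. If the interaction is fixed and kept, about 132 df remain and the issue is which effect the coefficients describe. The wording should be changed because the correction is cheap and removes the dependence on an unstable variance estimate or a pre-test. The factorial ANOVA and its stated power need no change on this account.

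**What to change.** In the Statistical analysis section:

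- Fit centre as a fixed factor (two indicators). As a stratification variable, it stays in the model and is exempt from the p > 0.05 drop rule.
- Estimate RAGT, fPT and their interaction from the model without a centre-by-intervention term.
- Report centre-by-intervention separately, as an exploratory check of whether the treatment effect is consistent across sites, with site-specific effects and 95% CIs. Its p-value must not choose the treatment model.

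The cost is about a sentence or two of wording and 2 of about 140 residual df; recruitment and data collection do not change. Two limits should be acknowledged. Site-specific intervals will be wide: with 48 children per site, about ± 1.98 × 2.89 = 5.7 points for the RAGT effect. Inference is to these three centres. Against a null about a population of centres, a fixed-centre test would also exceed 5% (about 10% and 25% at between-site SDs of 2 and 4 points), so results should not be presented as generalising over centres. Three sites could not support that wider claim with useful precision in any case.

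### The adjusted regressions drop terms at p > 0.05 with none exempted, so treatment terms and stratification factors can be removed and treatment estimates that survive selection can be biased

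*Protocol article*

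**What the plan says.** The Statistical analysis section of the protocol article has two layers.

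- **Factorial ANOVA.** For each change score and outcome, a two-factor ANOVA tests RAGT, fPT and their interaction, and group means are reported with 95% confidence intervals. No elimination rule is attached.
- **Mixed-effects regression.** For each outcome a further model has centre as a random effect, a centre-by-intervention interaction, and other important variables as covariates, with age and GMFCS level as examples. The next sentence sets the selection rule: "Variables will be dropped from the model one at a time if" p is above 0.05. The stated purpose is to assess "the effect of the interventions in the presence of important variables that were not balanced across intervention groups by randomization". These models are also said to cope with incomplete observation times.

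The Randomization section says that age, GMFCS level and site "will be used as stratification variables to ensure group balance".

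**The concern.** The elimination sentence speaks of variables in general. It does not set apart the treatment factors, their interaction, centre by intervention, or the factors used to stratify the randomisation. Age and GMFCS level are named as covariates, so they fall under the rule on any reading.

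Two things are at stake. First, a treatment estimate that is shown only when its p-value is at most 0.05 is too large on average, and the usual confidence interval takes no account of how it was chosen. Second, the final model is settled by the data, outcome by outcome, so adjusted results for different outcomes need not answer the same question. The adjusted models are the only ones said to allow for important covariates, centre effects and incomplete follow-up, and the Sample size section expects 10% drop-out. Readers are therefore likely to treat their estimates as the adjusted trial results.

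**Working it through.** **Inputs (Sample size section).** The calculation is made "assuming a Type I Error of 0.05 and 36 patients per group", with 85% "power to detect an effect size of 0.25 for the RAGT group, 0.25 for the fPT group, and 0.25 for the interaction". It continues "Assuming a standard deviation (SD) of subjects of 10", and "these effect sizes correspond to an actual SD among appropriate means of 2.5". It also notes that "a change of 3 points on the GMFM-66 is considered a clinically important difference".

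**1. The plan's own figure.** N = 4 × 36 = 144. Noncentrality = N × f² = 144 × 0.25² = 9.0, with 1 and 140 degrees of freedom. Power = 84.6%, so the stated 85% reproduces. An SD of 2.5 among two means is a 5-point difference between the levels of one factor. A two-sample check (72 v 72, difference 5, SD 10) gives 85.1%.

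**2. What a treatment term needs to survive.** The RAGT main effect compares 72 with 72 children.
- Standard error = 10 × √(2/72) = 1.667.
- Critical t on 140 df = 1.977.
- Survival threshold = 1.977 × 1.667 = 3.30 points.

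An estimate exactly equal to the 3-point clinically important difference would be removed.

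**3. Size of the bias, closed form, true effect 3.** z = (3.295 − 3)/1.667 = 0.177.
- P(kept) = P(Z > 0.177) = 0.430.
- Mean kept estimate = 3 + 1.667 × φ(0.177)/0.430 = 3 + 1.667 × 0.393/0.430 = 4.52.

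**4. Simulation with every term eligible.** 36 per arm, SD 10, 4,000 trials per row, one-at-a-time removal over RAGT, fPT, RAGT*fPT, age and GMFCS level. The following are assumptions, not figures from the document: fPT effect 3, interaction 0, age effect 3, GMFCS effect 5, balanced strata, ordinary least squares, no centre terms.

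| True RAGT effect | RAGT kept | Mean kept estimate | 95% CI coverage when kept |
|---|---|---|---|
| 0 | 5% | not meaningful (both signs) | 0% |
| 1.5 | 15% | 3.97 | 79% |
| 3 | 44% | 4.56 | 94% |
| 5 | 84% | 5.47 | 97% |

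If the interaction is removed before the main effects are considered, and no covariates are included, a true effect of 3 gives RAGT kept in about 46% of trials, a mean kept estimate of 4.3 to 4.4, and coverage of 91% with 0/1 coding. Across these variants the kept estimate is 4.3 to 4.6, that is 43% to 52% too large.

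An interaction contrast of 3 points, on the same scale as the main effects, is removed in 58% of trials.

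**5. Simulation with only age and GMFCS level eligible.** Same settings, with RAGT, fPT and RAGT*fPT forced in. At least one of age and GMFCS level is dropped in about 63% of trials. Mean RAGT estimates are −0.06, 1.50, 3.02 and 4.95 for true effects 0, 1.5, 3 and 5, with coverage of 94.6% to 95.2%. The bias is negligible.

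**The case against.** The strongest reply is that the treatment test is safe. The powered analysis is the factorial ANOVA, its terms are fixed, and each factor and group mean is reported whatever the p-value. That stands. A reader might infer that a non-significant therapy would end the trial with no estimate at all. The document does not support this; the gap is confined to the adjusted models.

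A second reply is that the treatment terms were surely meant to stay. The elimination sentence follows the mention of covariates, and the stated aim is to assess the interventions, which a model without them cannot do. This is a plausible intention, and under it the bias disappears (step 5). But the text does not say so, and even then the stratification factors can go and the models can differ by outcome.

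Two further inferences go beyond the text.

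- **Covariates chosen by observed imbalance.** Imbalance appears as the rationale. The removal criterion is the p-value, and age and GMFCS level are named in advance. The covariate list is left open, however, so the rationale could be used that way.
- **Loss of the interaction turning a 5-point arm effect into 2.5 in the full model.** Suppose all three active arms gain 5 points at SD 10. The interaction is dropped in about 68% of trials, but in those trials the full model with 0/1 coding gives about 4.1. Only the reduced additive model gives 2.5, and that is the factorial main effect the trial plans to test. With effect coding, dropping the interaction leaves the RAGT estimate unchanged. The document does not state the coding.

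Finally, an analysis plan not shown may hold the full covariate list. Its absence from the article is not held against the plan. The point concerns a rule that the article does state.

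**Conclusion.** The point holds for the adjusted mixed-effects regressions and not for the factorial ANOVA. The rule as written exempts no term, so treatment terms and the stratification factors age and GMFCS level can be removed, and the model can differ between outcomes.

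The size depends on the reading. If treatment terms are eligible, a true 3-point RAGT effect survives in about 46% of trials with a mean kept estimate of about 4.4. The excess is smaller for a true effect of 5 (about 9%) and larger for 1.5. If only covariates are eligible, bias and loss of coverage are negligible, and the remaining fault is that the model is not fixed in advance and stratification factors may be left out.

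The figures rest on the plan's SD of 10 and 36 per arm, no interaction, balanced strata, and least squares without centre terms. They show the direction and rough size of the effect, and do not predict this trial's results.

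**What to change.** In the Statistical analysis section:

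- Delete the p > 0.05 elimination rule.
- State that RAGT, fPT, RAGT*fPT, age stratum, GMFCS level and centre stay in the adjusted model for every outcome, whatever their p-values. Centre is already there as a random effect.
- Name any further covariates in advance, and reword the rationale so that observed imbalance is not a ground for choosing them.
- Test centre by intervention once, as a separate check of heterogeneity that does not alter the main model.
- Keep the residual diagnostics.

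The cost is wording plus a few degrees of freedom out of about 140 (144 − 4). No change to recruitment, data collection or the factorial ANOVA is needed.
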